**Reporting Procedures**

All adverse events will be reported. Depending on the nature of the event the reporting procedures below will be followed.

**Non serious AEs**

All such events, whether expected or not, will be recorded.

**Serious AEs**

An SAE form will be completed within 24 hours of the research team becoming aware of the event.

All SAEs will be reported to the Hertfordshire REC where in the opinion of the Chief Investigator, the event was:

- ‘related’, *ie* resulted from the administration of any of the research procedures; and
- ‘unexpected’, *ie* an event that is not listed in the protocol as an expected occurrence

Reports of related and unexpected SAEs will be submitted within 15 days of the Chief Investigator becoming aware of the event, using the COREC SAE form for non-IMP studies.

#### Statistics & Data Analysis

#### Data analysis

The primary outcome measure for the intra-arterial infusions studies will be percentage change in the forearm blood flow ratio and/or absolute flow in the infused arm. Absolute forearm blood flow in each arm, blood pressure and heart rate will also be reported.

Significance will be determined using ANOVA and paired Student’s t tests, corrected for multiple comparisons where indicated.

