**Hypotheses**

1. Dietary supplementation with a standardised tomato extract product improves endothelial function in healthy older people and patients with stable cardiovascular disease.
2. Dietary supplementation with a standardised tomato extract product improves parameters of arterial stiffness.
3. Dietary supplementation with a standardised tomato extract product reduces lipoprotein oxidation and circulating markers of endothelial damage.

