**Study Design**

Subjects will be screened, then randomised to receive Ateronon or placebo for 56 days. Randomisation will be unequal for each group (ratio 2:1 drug:placebo). Forearm plethysmography studies will be conducted pre-dose and at the end of the treatment period. Arterial stiffness will also be measured at both study visits.

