#### Power calculations

In each group (i.e. healthy older or stable CVD), up to 30 subjects will provide 90% power (P<0.05, 2 sided) to detect a 20% change in forearm blood flow (SD 0.25, α=0.05).

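### The protocol lets paired t tests decide significance and never says that the treatment question is answered by comparing tomato extract with placebo

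*Protocol*

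**What the plan says.** The Study Design section describes a parallel-group trial: "Subjects will be screened, then randomised to receive Ateronon or placebo for 56 days", allocated 2:1, which Figure 1 turns into 24 tomato extract and 12 placebo in each of the two groups. On timing it says: "Forearm plethysmography studies will be conducted pre-dose and at the end of the treatment period".

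The Data analysis section gives the outcome for the infusion studies as "percentage change in the forearm blood flow ratio and/or absolute flow in the infused arm" and then says: "Significance will be determined using ANOVA and paired Student’s t tests, corrected for multiple comparisons where indicated". The ANOVA has no stated factors, and neither test is tied to a particular question.

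No other section states the contrast. The first hypothesis reads "Dietary supplementation with a standardised tomato extract product improves endothelial function in healthy older people and patients with stable cardiovascular disease" and names no comparator. The Power calculations section refers to a change in flow with one SD, and mentions neither the arms nor the 2:1 ratio.

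**The concern.** A placebo-controlled trial answers its question through the difference between randomised arms. A paired t test from Visit 2 to Visit 3 within one arm measures everything that changed over eight weeks: the product, familiarity with an invasive procedure, season, regression to the mean. A paired test of an infusion against its own baseline within a visit shows only that the challenge agent altered flow. Neither involves placebo.

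Because the protocol names paired tests among those that determine significance, an analyst could follow it faithfully and report a significant rise in the tomato arm as support for the primary hypothesis. The related argument, that one arm changed significantly and the other did not, is also open. The 2:1 split favours that pattern, because the same drift reaches significance less often in the smaller placebo arm.

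**Working it through.** **Inputs from the protocol.** 24 tomato and 12 placebo completers per group (Figure 1); target change 0.20, SD 0.25, two-sided alpha 0.05, 90% power with up to 30 subjects (Power calculations). **Assumptions.** Approximately normal changes; a drift common to both arms, shown over a range because the documents give none; and, where stated, what the SD of 0.25 refers to.

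**1. The plan's own figure.** Take 0.25 as the SD of the change. For a two-sample t test the noncentrality is 0.20 / (0.25 × √(1/n1 + 1/n2)).
- 20:10 (30 subjects at 2:1): 2.07, power 51%.
- 24:12: 0.20 / (0.25 × 0.3536) = 2.26, power 59%.
- 30 per arm: 3.10, power 86%.

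For a paired t test the noncentrality is (0.20/0.25) × √n. Power is 91% at n = 19, 92% at n = 20 and 99% at n = 30. The stated 90% is therefore not reproduced exactly by either reading at 30, but of the readings tried only before-after ones reach 90% within 30 subjects.

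**2. Within-arm testing when the product does nothing.** Let e be the common drift in units of the SD of change. U(n, e) is the chance that a paired t test is significant in the direction of improvement (upper 2.5% tail, noncentrality e × √n). The arms are independent, so P(tomato significantly improved, placebo not) = U(24, e) × [1 − U(12, e)].

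| Drift e | Points, if SD of change = 25 | U(24) | U(12) | Tomato yes, placebo no |
|---|---|---|---|---|
| 0 | 0 | 0.025 | 0.025 | 2.4% |
| 0.1 | 2.5 | 0.068 | 0.050 | 6% |
| 0.2 | 5 | 0.154 | 0.092 | 14% |
| 0.4 | 10 | 0.467 | 0.244 | 35% |

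For example, at e = 0.4: 0.467 × (1 − 0.244) = 0.353. With 18:18 the corresponding figure at e = 0.4 is 23%, so the assumed drift accounts for more of the 35% than the unequal split does.

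**3. Between-arm testing under the same drift.** The drift is in both means and cancels in their difference. In 100,000 simulated trials at each of five drifts from 0 to 0.8 SD, the two-sided rejection rate stayed between 4.9% and 5.1%.

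**4. What baseline adjustment adds at 24:12.** Let r be the correlation between visits.
- If 0.25 is the SD of change, the ANCOVA SD is 0.25 × √((1 + r)/2). At r = 0.5 this is 0.217, power 72%; at r = 0.7 it is 0.230, power 66%. Both compare with 59% for the change score.
- If 0.25 is the SD at one visit, the change SD is 0.25 × √(2(1 − r)) and the ANCOVA SD is 0.25 × √(1 − r²). At r = 0.5 these are 0.250 and 0.217, power 59% and 72%. At r = 0.7 they are 0.194 and 0.179, power 81% and 87%.

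**The case against.** The strongest reply is that the sentence can be read innocently. Figure 2 defines BL3, BL5 and BL7 as agent-specific baselines for acetylcholine, nitroprusside and L-NMMA, each followed by two doses in the same person. The sentence on significance also comes straight after text about the infusion studies. Paired tests of infusion against baseline are a natural use there, and the ANOVA, named first, could carry a treatment factor.

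Much of this stands. A reader might infer that Visit 2 against Visit 3 is the only pairing available; Figure 2 shows that it is not. A reader might also infer that the plan is to bypass placebo. The protocol does not say that, and an ANOVA with a treatment factor is compatible with its wording. Nor does the power statement prove that a before-after test was intended, since no such reading reproduces 90% exactly at 30.

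Three further points are fair. ANOVA factors and covariates are commonly left to an analysis plan, so the absence of a baseline covariate is not an error, and analysing change is unbiased under randomisation. The drift is assumed, and 0.4 SD (10 points if the SD of change is 25) is half of the whole 20% target. A hypothesis without a named comparator is no fault when the design supplies one.

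The core remains. The protocol itself fixes paired tests as deciding significance, does not confine them to within-visit use, and nowhere makes the comparison with placebo decisive. A within-visit paired test would not supply that comparison either, nor would a correction for multiple comparisons.

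**Conclusion.** The concern holds as a defect of specification: the protocol does not say which test answers the treatment question, and one of the two that it names cannot do so in this design. Following the text therefore permits a within-arm change to be claimed as an effect.

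The size depends on a drift that the documents do not give. The misleading pattern rises from its nominal level of about 2.5% to 6%, 14% and 35% at 0.1, 0.2 and 0.4 SD. These figures illustrate what the wording allows; they do not predict what this trial will show. Adjustment for Visit 2 is a gain in efficiency, and its size depends on r and on which SD the 0.25 is.

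**What to change.** State in the Data analysis section that, in each group, the primary significance test is the tomato-minus-placebo difference in the Visit 3 acetylcholine response, from an ANCOVA adjusted for the Visit 2 response, reported with a 95% confidence interval. Add that paired tests are limited to descriptive within-arm or within-visit use and do not establish a treatment effect. Apply the same model to the nitroprusside and L-NMMA responses, augmentation index and pulse wave velocity.

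The model cannot be run until the acetylcholine response is one variable. Two doses are infused, and the outcome is worded as flow ratio and/or absolute flow, so one dose (or one dose summary) and one flow measure must be named.

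The cost is a short paragraph of text and no extra data, since both visits are already measured. The downside is that the 90% power claim must be restated for this between-arm contrast at 2:1, with the SD identified as that of a change or of a single visit. At 24:12 every case worked above falls short of 90%.

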**‘Healthy’**

- 30-80 years
- Non-smoking
- No hypertension/CVD
- No renal/respiratory/

neurological disease

- No diabetes

24 tomato extract o.d.

12 placebo o.d.

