**Number of Participants**

a) Sufficient numbers will be recruited to complete 36 healthy older male or female subjects (‘Healthy Group’)

AND

b) Sufficient numbers will be recruited to complete 36 stable cardiovascular disease patients on stable statin therapy (‘Stable CVD Group’).

Subjects will be asked to continue their intake of tomato and tomato based products as before (*i.e.* not to change their intake whilst on the study) to reduce interference with the study question. Other potential confounding effects of vascular function *e.g.* glucose, lipid profile and blood pressure will also be measured.

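### The protocol lets paired t tests decide significance and never says that efficacy rests on extract versus placebo, so a shift common to both arms could be declared an extract effect

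*Protocol*

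**What the plan says.** The Study Design section describes a parallel-group trial: "Subjects will be screened, then randomised to receive Ateronon or placebo for 56 days". It adds "Randomisation will be unequal for each group (ratio 2:1 drug:placebo", and the design figure gives 24 on extract and 12 on placebo in each of the Healthy and Stable CVD groups. The primary measurement is taken twice: "Forearm plethysmography studies will be conducted pre-dose and at the end of the treatment period".

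The Data analysis section defines the primary measure as the percentage change in forearm blood flow ratio and/or absolute flow in the infused arm, and then states: "Significance will be determined using ANOVA and paired Student’s t tests, corrected for multiple comparisons where indicated". It gives neither the factors of the ANOVA nor the contrast that the paired tests serve.

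No other section fills the gap. The hypotheses and the objective say only that supplementation improves function. The Power calculations section says that "up to 30 subjects will provide 90% power (P<0.05, 2 sided) to detect a 20% change in forearm blood flow" and mentions neither placebo nor the 2:1 split.

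**The concern.** Each participant receives one treatment only, so a paired test across visits is Visit 3 against Visit 2 within an arm. Such a test attributes to the extract anything else that moves between the visits, for example habituation to a second arterial cannulation, season, or residual operator or laboratory drift. The placebo arm is there to remove those influences, and a paired test makes no use of it.

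The unequal allocation adds an asymmetry. The same drift reaches significance more often in 24 people than in 12, so the pattern of a significant change on extract and a non-significant one on placebo can arise with no difference between treatments. That pattern is not a test of extract against placebo. At stake is the main conclusion of the trial: as written, the section would allow an efficacy claim to rest on an uncontrolled before-after change.

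**Working it through.** **Inputs.** From the protocol: 24 active and 12 placebo per group (Study Design figure); effect 0.20, SD 0.25, two-sided alpha 0.05, up to 30 subjects and 90% power (Power calculations). Assumed: SD 0.25 is the SD of the Visit 2 to Visit 3 change (the protocol does not say what it refers to; a per-visit SD of 0.25 with correlation 0.5 would give the same value). Also assumed: common drift of 0.01, 0.05 or 0.10 on that scale, and no drug effect.

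**Step 1: the protocol's own figure.** For a between-arm t test of change, the noncentrality is 0.20 / (0.25 × √(1/n₁ + 1/n₂)).

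- 20 v 10: 0.20 / 0.0968 = 2.07 on 28 df, power 51%.
- 15 v 15: 0.20 / 0.0913 = 2.19 on 28 df, power 56%.

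For a paired t test, the noncentrality is (0.20 / 0.25) × √n.

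- n = 20: 0.8 × 4.472 = 3.58, power 92.4%.
- n = 30: 0.8 × 5.477 = 4.38, power 98.9%.

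None of these returns 90% at 30 subjects, so the stated figure is not reproduced, and it does not identify which test was intended.

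**Step 2: paired test in the active arm, no drug effect, common drift δ.** The noncentrality is (δ / 0.25) × √24, and the test rejects when |t| exceeds 2.069 (23 df).

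| Drift δ | Noncentrality | Active arm (24) significant |
| --- | --- | --- |
| 0 | 0 | 5.0% |
| 0.01 | 0.04 × 4.899 = 0.196 | 5.4% |
| 0.02 | 0.08 × 4.899 = 0.392 | 6.6% |
| 0.05 | 0.20 × 4.899 = 0.980 | 15.6% |
| 0.10 | 0.40 × 4.899 = 1.960 | 46.7% |

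**Step 3: significant on extract, not on placebo.** The arms are independent, so the probabilities multiply. With 12 on placebo the paired test is significant in 9.7% of trials at drift 0.05 and 24.5% at 0.10.

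- Drift 0.05: 0.156 × (1 − 0.097) = 14%.
- Drift 0.10: 0.467 × (1 − 0.245) = 35%.

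**Step 4: between-arm test of change.** A common drift cancels in the difference between arms, so the false-positive rate does not depend on it. Simulation of 200,000 trials at 24 v 12 gives about 5% with and without drift.

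**Step 5: power of the between-arm test at the planned size.** 0.20 / (0.25 × √(1/24 + 1/12)) = 0.20 / 0.0884 = 2.26 on 34 df, power 59%.

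**The case against.** The strongest reply is that the sentence is ambiguous rather than wrong. The Forearm blood flow studies section creates paired data within each visit: each challenge agent has its own saline baseline, and both arms are measured at once. Paired tests may be meant to show that acetylcholine, nitroprusside or L-NMMA changed flow, with ANOVA carrying the treatment comparison, and assigning tests to contrasts is often left to the SAP. It stands that a paired test need not mean Visit 3 against Visit 2. But the within-visit contrasts do not compare extract with placebo either. The protocol itself says that paired tests determine significance and reserves no decision for a between-arm contrast, so this is more than missing detail.

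The size also has limits. The drifts are assumed, and inflation is slight when drift is slight (5.4% at 0.01, 6.6% at 0.02). A reader might infer that the error rate is far above 5% with any common drift; the calculation does not support that. Calibrated gauges, temperature control, challenge-specific baselines and the flow ratio reduce some sources of drift. Regression to the mean should not be listed among them, because no eligibility criterion selects on forearm blood flow.

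With no drift, having either test succeed gives 8.7% if neither is corrected, and about 4.5% if each is tested at 0.025. The multiplicity clause could therefore deal with that part. It cannot remove bias from a real drift.

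A reader might also infer from the power statement that a within-arm test was the planned main test, since 20 active participants give 92.4%. The section names no paired test and no active-arm subset, and 92.4% is not 90%. The inference is speculative and is not relied on here.

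**Conclusion.** The point holds in this form: the Data analysis section lets paired t tests determine significance, never states that efficacy rests on extract versus placebo, and no paired test in this design makes that comparison. With no drug effect, SD of change 0.25 and 24 active participants, the active-arm paired test is significant in 5.4%, 15.6% and 46.7% of trials at assumed drifts of 0.01, 0.05 and 0.10, against 5% for the between-arm test. These rates are illustrative because the protocol gives no drift. What does not depend on the values chosen is that the between-arm test is protected against common drift and the within-arm test is not. The documents do not show that the sponsor intends to decide efficacy by a within-arm test, only that the text permits it.

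**What to change.** In the Data analysis section, state that within each group (Healthy, Stable CVD) efficacy is judged only on the extract-minus-placebo difference with its 95% CI, for example from an ANCOVA of the Visit 3 response adjusted for Visit 2. Add that paired tests, across visits within an arm or within a visit, are supportive or descriptive and support no efficacy claim. Carry the same wording into the SAP.

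This is a short text change and needs no further data or participants. The cost is the loss of the within-arm route to significance. On the protocol's inputs, and taking SD 0.25 as the SD of change, the remaining between-arm test of change has about 59% power at 24 versus 12. The change of test does not create that weakness but makes it visible, so the power statement should be redone for the between-arm contrast at 2:1.

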#### Power calculations

In each group (i.e. healthy older or stable CVD), up to 30 subjects will provide 90% power (P<0.05, 2 sided) to detect a 20% change in forearm blood flow (SD 0.25, α=0.05).

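### The stated 90% power with up to 30 subjects per group is not supported for the extract-versus-placebo comparison that the 2:1 randomised design exists to make

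*Protocol*

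**What the plan says.** The Power calculations section of the protocol treats each population group (healthy older, stable CVD) separately and states that "up to 30 subjects will provide 90% power (P<0.05, 2 sided) to detect a 20% change in forearm blood flow", with "SD 0.25, α=0.05". It does not say whether the change is a difference between arms or a change within subjects. It gives no unit for the SD and does not say whether the SD belongs to one visit or to a change between visits.

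The Study Design section says "Randomisation will be unequal for each group (ratio 2:1 drug:placebo". Figure 1 shows 24 on extract and 12 on placebo in each group. Number of Participants says "Sufficient numbers will be recruited to complete 36 healthy older male or female subjects", and for the other group "Sufficient numbers will be recruited to complete 36 stable cardiovascular disease patients on stable statin therapy". The Interim Analysis section looks at 15 participants per group and considers a further 21, which again makes 36.

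The Data analysis section names ANOVA and paired t tests. It does not say which of these was powered, and it mentions neither baseline adjustment nor a between-visit correlation.

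**The concern.** A trial that randomises to extract or placebo answers its question through the contrast between those arms, and a power statement should describe that contrast. On the effect and SD given, the standardised effect is 0.8. Thirty subjects split 2:1 look far too few for 90% power to detect it.

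The stake is how the result is read. If power is nearer 59% than 90%, a true 20-point benefit would be missed in about 4 of 10 such trials in each group. A null result could then be taken as evidence of no effect from a well-powered study. The procedure is invasive (brachial artery cannulation at two visits), so those who approve or join the trial should also have a sound figure.

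**Working it through.** **Inputs (all from the protocol).** Effect 0.20 and SD 0.25, taken to be on the same scale; two-sided alpha 0.05; 30 subjects (Power calculations); 2:1 allocation (Study Design); 36 completers as 24 and 12 (Number of Participants, Figure 1). No dropout allowance is needed because the 36 are completers.

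**Assumption.** 0.25 is the SD of the quantity analysed. Step 4 relaxes this.

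**Step 1: trying to reproduce 90%.** Standardised effect: 0.20/0.25 = 0.8.

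- Paired (one-sample) t test, noncentrality 0.8 × √n. For n = 20: 0.8 × √20 = 3.58, critical t (19 df) 2.093, power 92.4%. For n = 19, power is 90.9%. For all 30 subjects, extract and placebo mixed, it is 98.8%.
- Two-sample t test with 30 per arm: 86.1% (normal approximation 87.3%).
- Two-sample t test pooling both populations at 48 against 24: 88.4%.

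The first route, restricted to the extract arm, would explain 30: about 19 to 20 extract subjects correspond to 29 to 30 in total at 2:1. The other two come near 90% but do not match a statement about up to 30 subjects in each group.

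**Step 2: power between arms.** Noncentrality = 0.20 / (0.25 × √(1/n₁ + 1/n₂)), with n₁ + n₂ − 2 degrees of freedom.

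- 20 against 10: standard error 0.25 × √(1/20 + 1/10) = 0.0968; noncentrality 2.066; critical t (28 df) 2.048; power **51.4%**.
- 24 against 12: standard error 0.25 × √(1/24 + 1/12) = 0.0884; noncentrality 2.263; critical t (34 df) 2.032; power **59.4%**.

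The normal approximation gives 54.2% and 61.9%. An equal split of 30 (15 against 15) gives 56.2%. A one-sided test at 20 against 10 gives 64.4%. None approaches 90%.

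**Step 3: what 90% would require.**

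| Quantity for 90% power, 2:1 | 20:10 | 24:12 |
|---|---|---|
| Detectable difference at SD 0.25 | 32.5 points | 29.5 points |
| SD needed for a 20-point difference | 0.154 | 0.170 |

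At an effect of 20 points and SD 0.25, 90% power needs 52 against 26, or 78 completers per population group (power 90.8%).

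**Step 4: if 0.25 is a single-visit SD.** With between-visit correlation r, the SD of the change is 0.25 × √(2(1 − r)), and the residual SD after baseline adjustment (ANCOVA) is 0.25 × √(1 − r²). Power from the same t formula:

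| r | Change, 20:10 | Change, 24:12 | ANCOVA, 20:10 | ANCOVA, 24:12 |
|---|---|---|---|---|
| 0 | 29% | 34% | 51% | 59% |
| 0.5 | 51% | 59% | 63% | 72% |
| 0.7 | 73% | 81% | 80% | 87% |
| 0.8 | 88% | 94% | 91% | 96% |

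Reaching 90% takes r of about 0.74 (ANCOVA) or 0.77 (change) at 24:12, and about 0.79 or 0.81 at 20:10.

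**Step 5: if 0.25 is the SD of change and the analysis adjusts for baseline.** The residual SD is 0.25 × √((1 + r)/2). At 24:12 this gives 72% power for r = 0.5 and 64% for r = 0.8.

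**Step 6: sample size.** Power calculations has up to 30; Number of Participants has 36; Interim Analysis has 15 + 21 = 36.

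**The case against.** The best defence is that the sentence speaks of a change and the protocol names paired t tests. Read as a before-after test in the 20 extract subjects, 90% is fair arithmetic. That may well be its origin, and if so the sum is right and the comparison is wrong. It does not rescue the claim: a within-arm test makes no use of the placebo group and cannot separate the supplement from repeat-visit effects, regression to the mean or a placebo response.

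The second defence is that the SD is undefined. This stands as a limit on certainty. A reader might infer that the trial's power simply is 51% or 59%. The protocol does not support that flat statement, because those figures hold only if 0.25 is the SD of the analysed quantity. A single-visit SD with a high enough correlation would give 90%, but the protocol states no correlation.

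A reader might also infer that the paired test is the only route near 90%. It is not: pooling both populations gives 88% and 30 per arm gives 86%. Neither fits a statement made for each group with 2:1 allocation.

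Finally, the gap between 30 and 36 does not itself reduce power, since the planned number is the larger one. It is a smaller inconsistency, though dropout cannot explain it because the 36 are completers.

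**Conclusion.** The power statement is wrong as written for this design. With 0.25 as the SD of the analysed quantity, the shortfall from 90% is about 39 percentage points at 30 subjects and 31 at 36, too large to be due to rounding or to the choice between t and normal calculations. The firm conclusion is that the protocol's stated inputs do not support 90% power between arms. The particular values of 51% and 59% rest on the SD assumption, on an unadjusted two-sample comparison, and on each group reaching the stated number. If a group stopped at the interim look with 15 subjects (10 against 5), power on the same assumptions would be about 27%.

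It would go too far to conclude that the two populations must be pooled. The protocol sizes each group separately and defines them as distinct, with statin use excluded in the healthy group. A pooled primary test would change the primary question.

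**What to change.** Rewrite the Power calculations section for the comparison of extract with placebo at 24 against 12 in each group:

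- State what the SD of 0.25 refers to (one visit or change between visits) and on what scale.
- Replace 90% with the recomputed figure. If 0.25 is the SD of the analysed change, that is about 59% unadjusted power for a 20-point difference, or 90% power for a difference of about 29.5 points.
- If the comparison will be baseline-adjusted, give its power together with the assumed between-visit correlation.
- Use 36 per group throughout in place of 30.

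This changes wording only and needs no extra subjects. The cost is a less favourable power figure on the page. Keeping a 20-point target at 90% power without adjustment would instead take about 78 completers per group.

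A primary test across both populations (48 against 24, stratified by group) is an option for the sponsor and not part of the required correction. It has about 88% power unadjusted, but it assumes broadly similar effects in the two groups and would be a substantive amendment to the primary analysis.
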